### Interventions

2.3

#### Treatment as usual (TAU)

2.3.1

Individuals in the community who need support adhering to their ART can receive adherence counseling from HIV counselors at a local clinic in the community. We elected to use TAU as our study comparator given that this is the most likely alternative for accessing care outside of the study. For the current study then, couples who are randomized to TAU receive referrals to the local clinic for ART adherence support, other HIV-related services, or additional healthcare needs.

#### START Together

2.3.2

The 5-session intervention is based on the principles of cognitive-behavioral couple therapy (CBCT) applied to HIV treatment [7] and Life Steps for ART adherence [23]. CBCT is behavioral therapy approach focused on skills training in order for couples to improve communication and problem-solving skills, with the ultimate goal of improved relationship functioning [24]. The principles of CBCT (i.e., working with dyads, skills training related to communication and problem-solving) have been applied to the treatment of numerous medical problems including hypertension, diabetes, and chronic obstructive pulmonary disease [25]. Uthando Lwethu, a CBI with South African couples to promote couples HIV counseling and testing, used communication and problem-solving skills as central components and showed significant improvements in rates of couples testing for HIV together [10].

Formative work for the current intervention revealed the acceptability of learning and using couple-level communication and problem-solving skills in a therapeutic setting (i.e., with a counselor) by both women and men [26]. Furthermore, the intervention incorporates Life Steps, a one-session intervention based on the principles of problem-solving therapy [23]. It focuses on identifying barriers to ART adherence as well as feasible solutions in the form of devising plans and back-up plans. Life Steps has been adapted for the South African context [27] and has previously been used to promote ART adherence in individuals with depression [28] and substance use [29] in South Africa. Life Steps has previously been adapted for delivery to dyads as an optional session for PrEP adherence in Uganda [30] and in the US for serodiscordant male couples [31].

For the current study, the intervention has 5 sessions of fixed content. However, couples can complete up to 3 additional booster sessions (i.e., 8 sessions total), depending on the couple's preference or need for additional support. This is decidedly jointly with the intervention provider (i.e., interventionist). Couples who enroll in treatment for more sessions spend more time addressing barriers to ART adherence or other HIV or relationship issues. Both partners must be present for a session to be carried out—couples are made aware of this during the informed consent process. Intervention sessions take between 60 and 75 min. Table 2 presents an overview of the content for the 5-session intervention.

**Table 2 tbl2:** Intervention content for START Together.

Session	Treatment content	Homework
1	- Provide psychoeducation on symptoms, etiology, and treatment for HIV - Disabuse misconceptions about HIV transmission and infection - Describe impact of HIV on couple's relationship - Elicit individual and couple-level goals for treatment - Highlight the importance of homework assignments	

2	- Teach couple communication skills (sharing thoughts and feelings technique) - Couple practices communication skills on HIV-related topic	- Practice sharing thoughts and feelings technique on topic of choice related to HIV (low to moderate emotional intensity)

3	- Homework check-in - Discuss Life Steps to identify most challenging barriers to ART adherence - Teach couple-level problem-solving skills - Couple uses couple-level problem-solving skills to address one barrier from Life Steps	- Implement plan from Life Steps to address barrier to ART adherence - Practice problem-solving skills on another Life Steps barrier or another topic of choice related to HIV (low to moderate emotional intensity)

4	- Homework check-in - Use Life Steps and couple-level problem-solving to address additional barriers to ART adherence or other issues related to HIV (e.g., maintaining a safe and fulfilling sexual/physical relationship, decision to disclose HIV status to others)	- Implement solution to problem identified in session - Practice sharing thoughts and feelings technique or problem-solving on a topic of choice related to HIV (low to moderate emotional intensity)

5	- Homework check-in - Discussion of treatment successes and relapse prevention - Couple problem-solves barriers to maintaining gains from treatment or dealing with lapses/relapses - Couple identifies and discusses areas for desired future growth (their own or dyadic) and decides whether additional treatment sessions would be helpful	- Continue practicing new learned behaviors, including communication and problem-solving skills, as well as the devised plans to address ART non-adherence or other HIV-related issues

6–8 (booster sessions)	- Continued use of communication and problem-solving skills to address issues related to ART adherence, HIV, or the couple's relationship more broadly	- As needed, depending on the issues discussed in session

### Intervention providers

2.4

#### Selection, training, and supervision

2.4.1

Providers for the intervention hold a Masters degree in psychology and have experience providing clinical services for mental health. Initial training in the intervention involves a 3-day training led by the intervention developer ([name]). The training is based on previous CBI trainings with regard to content, length, and format [32]. The training involves a mix of didactics and role plays. Core concepts discussed include the CBCT model, core intervention strategies (Life Steps, communication, and dyadic problem-solving), and clinical strategies to deal with challenging couples. After the initial training, interventionists complete ongoing practice with two mock cases, which is discussed in weekly supervision. One session from each interventionist is coded for content and process fidelity (e.g., appropriate handling of couple arguments). Interventionists are required to score a 75% on fidelity to begin providing treatment.

Ongoing supervision is provided weekly (1 hour) using group supervision. The interventionist provides an English audio recording or transcription of a segment of the session, which is then reviewed by the supervisor. Verbal updates on couples whose sessions are not translated are also discussed. Feedback based on fidelity to intervention session content and process is provided. Interventionist questions regarding specific couples are also addressed. A multicultural lens is used during supervision as a framework to support differing cultural backgrounds and perspectives of the interventionist, couples, and supervisor, and facilitates open discussion about these issues in supervision [33,34].

### Measures

2.5

#### Implementation outcomes

2.5.1

***Feasibility.*** Defined as the suitability, fit, or utility of the intervention in the current setting [35]. This is measured using (1) the percentage of couples assigned to START Together who agree to enroll in the intervention and (2) a 14-item feasibility subscale of a validated implementation science measure designed for pragmatic mental health interventions in global low-resource settings [36]. Only couples randomized to START Together complete the feasibility measure and patients and partners complete the form separately at 8-weeks.

***Acceptability.*** Defined as the tolerability or satisfaction of the intervention [35]. This is measured by (1) assessing couple's attendance and retention in the intervention and (2) a 15-item acceptability subscale of the validated implementation science measure designed for global low-resource settings [36]. Only couples randomized to START Together complete the acceptability measure and patients and partners complete the form separately at 8-weeks.

***Fidelity.*** A randomly selected subset (20%) of the intervention sessions are translated from isiZulu to English and rated for fidelity by an independent rater who is trained in the protocol. The rater assesses content fidelity specific to the intervention, adapted from fidelity for a CBCT for depression intervention in a high-resource setting [37], as well as process fidelity (e.g., verbal communication, being non-judgmental) adapted from prior research on common therapist factors in low-resource settings [38].

#### Efficacy outcomes

2.5.2

***Women's ART adherence.*** The amount of HIV viral copies extracted from medical records (past 30 days) or dried blood spots is used as an indicator of adherence to ART. A viral load of <50 c/mL is considered virally suppressed according to South African guidelines [19]. This is supplemented with participants' self-report of adherence to ART using the 3-item Ira Wilson adherence measure [39], which has been previously used in South Africa [40,41]. Blood samples are stored in a secure area at the Human Sciences Research Council and are tested by a local laboratory service. Viral load is collected at baseline and 12-weeks and self-report ART adherence is collected at baseline, 8-weeks, and 12-weeks.

***Men's engagement in HIV care.*** Dichotomous engagement in care (yes/no) is extracted from men's clinical records (if available) and supplemented with self-report at 12-weeks. Appropriate engagement in care depends on men's HIV status and current level of engagement. For men who are HIV-negative, receiving an HIV-test after 3 months is appropriate engagement in care. For men who are living with HIV but are not taking ART, initiating ART is the next appropriate step in the HIV care cascade. For men living with HIV who take ART but are not virally suppressed, improving adherence and achieving viral suppression is the next level of care engagement. Regardless of men's initial level of care engagement, achieving the next milestone in the HIV care cascade is recorded as positive for engagement in care.

***Couple's relationship functioning.*** A 39-item self-report measure assessing factors of relationship functioning was developed based on qualitative work assessing local definitions of healthy relationships with men and women in committed relationships from Cape Town and Vulindlela communities [42,43]. The factors are active relationship building, open communication, and couple-level problem-solving.^1^ Preliminary quantitative data from this measure show adequate reliability of the constructs, with alpha values ranging from .69 to .81 [44]. Assessment occurs at baseline, 8-weeks, and 12-weeks.

## Data plan and management

3

### Power, sample size, and data analysis

3.1

The primary efficacy outcome, for which a power analysis can be calculated, is women's viral suppression. Only one prior study examined the efficacy of a CBI for ART adherence with serodiscordant couples in the US and found that after a 4-session intervention, 47% of the intervention group compared to 25% of the control group (who received referrals to medical provider) had at least 90% adherence to their ART [45]. Based on this, a power analysis was conducted using G*Power 7 [46] comparing the proportion of the sample reaching viral suppression between the two treatment arms.^2^ Using a two-tailed test and equal allocation of the sample between the two treatment arms, to achieve a power of .80 would require a total *N* = 148 (*n* = 74 in each arm). Because the current study is a pilot trial focused on feasibility and acceptability of the proposed intervention and collecting preliminary efficacy data on the intervention, our sample size will be *N* = 20 couples (*n* = 10 couples in each arm). A sample size of 20 represents the smallest sample size deemed appropriate for any statistical modeling [47]. The study will therefore be underpowered to detect significant differences between study arms in the efficacy outcome. We will instead focus on the direction of effects.

Descriptive statistics will be reported for implementation outcomes. For feasibility and acceptability, the proportion of the sample meeting the definitions used to define these constructs (see Measures) will be reported. Means, standard deviations, and ranges will be reported for the self-report measures of feasibility and acceptability, as well as for fidelity. We will compare these descriptives to previous behavioral couple- and family-based interventions in sub-Saharan Africa [10,48].

To analyze the efficacy outcomes, we will use an intent-to-treat analysis, where all individuals will be analyzed according to the condition to which they were randomized. Generalized linear mixed models (GLMM) will be used to compare the two treatment arms (START Together vs. TAU) over time on women's ART adherence, men's engagement in care, and couple's relationship functioning. GLMM increases power by including all available data points and is appropriate for continuous, dichotomous, and proportional variables [49]. We will compare the groups on relevant clinical and demographic factors (e.g., age) that exist between the two treatment arms. A priori, we do not plan to include clinical covariates in the analyses given the small sample size. Moreover, although we will not be able to statistically account for variability in session attendance in the START Together treatment arm (including whether or not booster sessions were attended), this information will be provided descriptively to aid in contextualizing the efficacy results.

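### One over-time mixed model is planned for all three efficacy outcomes, but men's engagement has a single 12-week value, and binary viral suppression in 10 women per arm can give infinite estimates

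*Protocol article*

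**What the plan says.** Under Power, sample size, and data analysis (3.1), the protocol article names one method for all efficacy outcomes: generalized linear mixed models that "compare the two treatment arms (START Together vs. TAU) over time on women's ART adherence, men's engagement in care, and couple's relationship functioning". It justifies the choice on the grounds that such models use every available data point and can handle dichotomous variables.

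Under Efficacy outcomes (2.5.2), the outcomes have different structures:

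- **Men's engagement:** "Dichotomous engagement in care (yes/no) is extracted from men's clinical records (if available) and supplemented with self-report at 12-weeks". The scoring is relative to where each man started: "Regardless of men's initial level of care engagement, achieving the next milestone in the HIV care cascade is recorded as positive for engagement in care".
- **Women's adherence:** "Viral load is collected at baseline and 12-weeks and self-report ART adherence is collected at baseline, 8-weeks, and 12-weeks". The viral measure is dichotomised: "A viral load of <50 c/mL is considered virally suppressed according to South African guidelines".
- **Relationship functioning:** a self-report scale at baseline, 8 weeks and 12 weeks.

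Section 3.1 also says: "The primary efficacy outcome, for which a power analysis can be calculated, is women's viral suppression". The sample is 20 couples, 10 per arm. The article accepts that this is underpowered and says attention will be on the direction of effects.

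**The concern.** The model named in 3.1 needs repeated measurements, and one of the three outcomes it is assigned to has none. For men's engagement the two sections do not agree, and whoever analyses the data will have to replace the stated method.

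For suppression the design does have two visits, but each arm-by-visit cell holds only 10 binary values. If nobody, or everybody, in a cell is suppressed, maximum likelihood has no finite log odds for that cell, and effects built on it have no usable size or standard error. Women are recruited for difficulty with HIV treatment, so a low baseline rate is possible. In both cases the replacement method would be chosen after the data are seen.

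**Working it through.** **1. The plan's own figure.** Inputs from 3.1: 47% and 25%, two-tailed, 1:1, power 0.80. The 5% level is assumed, as the article does not state alpha. With pooled variance under the null and mean proportion 0.36:

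n per arm = [1.96 × √(2 × 0.36 × 0.64) + 0.842 × √(0.47 × 0.53 + 0.25 × 0.75)]² / 0.22² = 73.5, rounded up to 74, total 148.

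This matches the stated 148, so the sample-size arithmetic is not in question. The rates 47% and 25% are reused below as the article's planning values for 12-week suppression.

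**2. Men's engagement.** There is one binary value per man, at 12 weeks. Because the value records progress since entry, it has no baseline counterpart, and no 8-week value is listed. A time term, or an arm-by-time term, therefore has nothing to act on.

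For the random intercept, take an illustrative result of 3/10 against 5/10. The maximised log-likelihood is 3 ln 0.3 + 7 ln 0.7 + 10 ln 0.5 = −13.0401. Refitting with the random-intercept SD fixed at 0, 0.5, 1, 2, 3 and 5 gives −13.0401 every time, while the log odds ratio moves from 0.85 (SD 0) to 2.78 (SD 5). The data cannot choose between these fits, so the random effect is not identified.

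**3. Viral suppression, 12-week cells only.** The chance that a cell of n women is empty or full is s(p, n) = pⁿ + (1 − p)ⁿ.

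- s(0.47, 10) = 0.0005 + 0.0017 = 0.0023
- s(0.25, 10) = 0.0000 + 0.0563 = 0.0563
- At least one of the two: 1 − (1 − 0.0023)(1 − 0.0563) = 0.058

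With 8 women per arm observed, the same formula gives 0.108.

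**4. Viral suppression, arm-by-time model with separate baseline cells.** Take a baseline rate p₀, the same in both arms. The article does not give it, so a range is shown.

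P = 1 − (1 − s(p₀, 10))² × (1 − 0.0023)(1 − 0.0563)

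| Assumed p₀ | s(p₀, 10) | P(at least one empty or full cell) |
|---|---|---|
| 50% | 0.0020 | 0.062 |
| 30% | 0.0283 | 0.111 |
| 20% | 0.1074 | 0.250 |
| 10% | 0.3487 | 0.601 |

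The formula is symmetric in p₀, so 70% gives 0.111 and 80% gives 0.250.

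**5. Sensitivity to independence.** The product treats the two visits as independent, although the same women contribute to both. Whatever the within-woman correlation, P lies between the larger of the baseline-only and 12-week-only probabilities and their sum. At 20% the baseline cells alone give 1 − (1 − 0.1074)² = 0.203, so P lies between 0.203 and 0.262. At 10% they give 0.576, so P lies between 0.576 and 0.634. The conclusion does not depend on independence.

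**6. Sensitivity to parameterisation.** If the model uses one common baseline for all 20 women, the baseline term becomes s(p₀, 20). At 10% this is 0.122, and P falls to 1 − (1 − 0.122)(1 − 0.058) = 0.17. At 20% it is 0.012, and P is 0.07.

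**The case against.** **The men's analysis still gives an answer.** Without the random effect and the time term, the model is an ordinary logistic regression of engagement on arm, finite unless a cell is empty or full. This stands. A reader might infer that men's engagement cannot be analysed at all; the article does not support that. What cannot be done is the over-time mixed model it names. The assessment schedule (Table 1) is not legible in the available text, but 2.5.2 gives only the 12-week time point for this outcome.

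**Suppression need not be sparse.** A reader might infer that the suppression model will often fail. The eligibility criteria do not imply this: self-reported difficulty or missed visits are enough for entry, so suppressed women can enrol. At 50% baseline suppression the risk is 6%, and 3.1 does not commit to separate baseline cells for each arm. This stands, and it limits the point to a conditional risk.

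**Only direction matters in this pilot.** This holds in part. With a single empty or full cell the direction is still determined, but size and precision are lost. If both arms have no suppressed woman at baseline, the interaction is a difference of two infinite quantities and even its sign is undefined. At 10% baseline suppression that has probability 0.349² = 0.12.

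**Sparse-data fallbacks and random-effect structure belong in an analysis plan.** This is fair for details left unstated. The point here concerns what 3.1 does state: one method for three outcomes. The same reasoning removes another tempting inference, that partner correlation in relationship functioning will be ignored and the error rate inflated. The article names a mixed model and nowhere says partners will be treated as independent, so no error-rate claim can be attached to it.

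**Conclusion.** The point holds in a limited form. For men's engagement, 3.1 and 2.5.2 are inconsistent regardless of any assumption: a single 12-week milestone cannot be modelled over time, and a per-man random intercept is not identified.

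For the primary efficacy outcome, the planned type of model can fail to give a finite estimate. The risk is about 6% from the 12-week cells alone at 47% and 25%. Under the separate-baseline model it ranges from 6% to 60% over assumed baseline rates of 50% down to 10%. These figures rest on the baseline rate, on complete data in 10 women per arm, and on using the article's adherence-based rates for suppression. They show a risk worth planning for, not an expected failure.

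Relationship functioning and self-reported adherence, each with three assessments, suit the planned model.

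**What to change.** Reword the analysis paragraph of 3.1 by outcome:

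- **Men's engagement:** compare the 12-week proportions between arms, as a risk difference with a Newcombe or exact unconditional 95% confidence interval.
- **Women's viral suppression:** make the same single-time-point comparison at 12 weeks. If an analysis adjusted for baseline suppression is wanted, use Firth-penalised logistic regression, which stays finite with empty or full cells.
- **Relationship functioning and self-reported adherence:** keep the mixed model over the three assessments.

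Other sound interval methods would also serve; what matters is that the choice is written down before the data are seen. The cost is a few sentences. No data collection, sample size or visit changes, and the simpler analyses suit a pilot that reports direction and rough size of effect.

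### Section 3.1 does not say how the baseline score enters the GLMM; conditioning on it would make the relationship-functioning and self-reported adherence comparisons modestly more precise at almost no cost

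*Protocol article*

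**What the plan says.** Section 3.1 (Power, sample size, and data analysis) sets the efficacy analysis: "Generalized linear mixed models (GLMM) will be used to compare the two treatment arms (START Together vs. TAU) over time", applied to women's ART adherence, men's engagement in care and relationship functioning. The reason given for the model is that "GLMM increases power by including all available data points and is appropriate for continuous, dichotomous, and proportional variables". After a sentence on comparing the arms on clinical and demographic factors such as age, the section states: "A priori, we do not plan to include clinical covariates in the analyses given the small sample size".

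Section 2.5.2 (Efficacy outcomes) gives the timing. For relationship functioning, "Assessment occurs at baseline, 8-weeks, and 12-weeks". For women's adherence, "Viral load is collected at baseline and 12-weeks and self-report ART adherence is collected at baseline, 8-weeks, and 12-weeks".

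The pilot has 10 couples per arm. Section 3.1 accepts that it is underpowered for efficacy and says how the results will be read: "We will instead focus on the direction of effects".

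**The concern.** Taken together, these statements most naturally describe a repeated-measures model with baseline as one of the outcome occasions and no covariates. If each arm has its own baseline mean, then with complete data the week-12 treatment contrast equals the difference between arms in mean change from baseline.

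That contrast uses the baseline score but does not condition on it. It subtracts the whole of any chance baseline difference. A regression on baseline subtracts only the share that is expected to persist (the correlation, when the variances are equal). The remainder is regression to the mean and goes into the estimate.

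With 10 couples per arm, sizeable chance differences at baseline are likely. Because the plan will read the direction of effects, extra variance bears directly on the quantity it means to interpret. The small sample is a sound reason not to add several clinical covariates, but it does not argue against using one prognostic baseline score efficiently.

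**Working it through.** **The plan's own figure.** The sample-size paragraph uses 47% against 25%, two-tailed, 80% power and 1:1 allocation. The significance level is not stated, so 0.05 is assumed. With pooled rate 0.36 and no continuity correction:

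n per arm = [1.96·√(2·0.36·0.64) + 0.8416·√(0.47·0.53 + 0.25·0.75)]² / 0.22² = (1.330 + 0.556)² / 0.0484 ≈ 73.5, so 74 per arm and 148 in total.

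This reproduces the stated figure. It concerns a binary outcome and does not depend on how baseline is handled.

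**Inputs for the baseline question.**
- n = 10 couples per arm (section 3.1).
- Baseline and follow-up scores on a continuous scale (section 2.5.2), taken as one score per couple with one follow-up and equal variance σ² at each visit (simplifying assumptions).
- Correlation ρ between baseline and follow-up: not given. The alpha values of .69 to .81 in section 2.5.2 measure internal consistency, not correlation over time. A range of 0.3 to 0.8 is assumed.

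**Formulas for the week-12 contrast.**
- Change from baseline (free baseline mean in each arm): variance = 2σ²(1 − ρ)·(2/n).
- Baseline as covariate: variance = σ²(1 − ρ²)·(2/n)·[1 + 1/(2n − 4)]. The last factor is the price of estimating the slope; at n = 10 it is 17/16.
- Ratio, adjusted to change = (1 + ρ)/2 × 17/16.

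Variances below are in units of 2σ²/n. Standard errors (SE) are in units of σ.

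| ρ (assumed) | Change, 2(1 − ρ) | Adjusted, (1 − ρ²)·17/16 | Ratio | SE change | SE adjusted |
|---|---|---|---|---|---|
| 0.3 | 1.40 | 0.967 | 0.69 | 0.529 | 0.440 |
| 0.5 | 1.00 | 0.797 | 0.80 | 0.447 | 0.399 |
| 0.7 | 0.60 | 0.542 | 0.90 | 0.346 | 0.329 |
| 0.8 | 0.40 | 0.382 | 0.96 | 0.283 | 0.277 |

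A simulation with 10 per arm and 20,000 runs agrees. The SEs for change and adjusted were 0.528 and 0.439 at ρ = 0.3, 0.444 and 0.397 at 0.5, and 0.347 and 0.327 at 0.7.

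**Chance imbalance.** The baseline difference between arms has standard error √(2/10) = 0.447 SD. Given a baseline difference d, the change contrast is shifted by −(1 − ρ)d. For d of one standard error and ρ = 0.5, the shift is −0.5 × 0.447 = −0.22 SD.

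**Effect on the sign.** Assume a true effect of 0.5 SD and a normal approximation. The chance of the wrong sign is Φ(−0.5/SE):
- ρ = 0.3: about 17% (change) and 13% (adjusted).
- ρ = 0.5: about 13% and 10.5%.
- ρ = 0.7: about 7.4% and 6.4%.

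**If the arms already share a baseline mean.** The GLMM is then about as precise as the covariate model, and there is essentially nothing to gain.

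**The case against.** The strongest objection is that the article does not describe the model criticised here. It names no arm-by-time term and no change-from-baseline effect, and it does not say whether baseline means are free or common. Its wording is compatible with a common-baseline model, under which the loss disappears. Such detail often sits in a full protocol or analysis plan, and neither is shown. This stands: the loss is conditional on the ordinary reading, and the article's silence on parameterisation is not itself a fault.

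A reader might infer from the covariate sentence that the plan makes no baseline adjustment, or excludes the baseline score. The documents do not support that. The sentence is limited to clinical covariates and follows one about clinical and demographic characteristics; it does not mention the baseline value of the outcome. Baseline scores also plausibly enter the model already, as repeated measures.

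A reader might also take from the table that the plan wastes the equivalent of about 25% more couples (1/0.797 = 1.255). That holds only at ρ = 0.5 under the unconstrained model. At ρ = 0.7 and 0.8 the corresponding figures are about 11% and 5%.

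Finally, the outcomes concerned are not the primary efficacy outcome, self-report only supplements viral load, and the article already says that conclusions about effect strength will be limited. That also stands and keeps the point small. It does not remove the case for the better estimator, which uses data the trial collects anyway.

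**Conclusion.** This is a nearly free improvement, not an error in the plan. If the GLMM is fitted in the ordinary way with a free baseline mean in each arm, the week-12 contrasts for relationship functioning and self-reported adherence are less precise than they need be. Conditioning on baseline brings the variance to about 0.69 of the change-score value at ρ = 0.3 and 0.96 at ρ = 0.8.

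The size rests on the assumed correlation, complete data, equal variances, a continuous couple-level score and a single follow-up. The benefit to the direction-of-effect reading is modest: between one and about four percentage points in the chance of a wrong sign for ρ of 0.7 down to 0.3, if the true effect is 0.5 SD. No figure in the article is shown to be wrong. Viral suppression and men's engagement are binary, and these calculations do not address them.

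**What to change.** Add a sentence to section 3.1 for relationship functioning and self-reported adherence, choosing one of two forms:
- keep baseline, week 8 and week 12 as outcomes in the GLMM and constrain the two arms to a common baseline mean; or
- model the week-8 and week-12 scores with the baseline score as covariate.

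Report the adjusted week-12 difference with its 95% confidence interval, so that the direction is read together with its uncertainty. Keep the decision to add no other clinical covariates.

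The cost is a line of wording and at most one degree of freedom, already counted in the 17/16 factor. No new data, visits or couples are needed. If the common-baseline form is already intended, the change is only to say so.
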